#### Phase 2: survey and interviews

Phase 2 will analyse what drives the differential usage of WACHS CC services across country WA by employing a cross-sectional survey and follow-up individual interviews, as part 1 and 2, to explore the behaviours, attitudes, and perspectives that front-line clinicians have for CC services, the reasons behind the differential use of services and contextual factors that may influence use. This also aims to elicit values and benefits front-line clinicians perceive when accessing CC services, and thoughts about improvements for future use.

#### Phase 2, part 1: survey

##### Survey instrument

Survey items, data collection, and analysis will be structured around the expanded RE-AIM and PRISM guidance,^
42
^ incorporating the normalisation process theory (NPT),^
43
^ and the Implementability of Healthcare Interventions.^
44
^

The survey will be divided into four parts:
1. Demographics2. Use of CC services.3. Perceptions (appropriateness, acceptability, and feasibility),^
45
^ behaviours, attitudes, and value towards using CC services.^
39
^4. Staff perception of the long-term sustainability and areas for improvement of CC services.^
40
^The survey will embed the Normalisation MeAsure Development (NoMAD) instrument,^
46
^ which covers four theoretical constructs based on NPT.^
43
^ These are coherence, cognitive participation, collective action, and reflexive monitoring and will be gathered in part 3 of the survey. NPT specifically provides greater understanding to the concepts of adoption, implementation, and maintenance (sustainment) from RE-AIM.^
47
^ Perceived risk has been shown to be a common barrier and precedent to the acceptance and adoption of technology and virtual healthcare services.^
48
^ Measures of risk to be included are based on Cunningham's^
49
^ major dimensions of perceived risk, plus additional categories appropriate to technology and service adoption.^
48
^ These categories are financial, performance, technological, psychological, social, physical, privacy, provider, and time. The three-item provider report of sustainment scale^
40
^ will be integrated into part 4 of the survey to assess sustainment.

The survey will be piloted with the research advisory team and 3 to 5 CC staff to ensure comprehension and ease of response. The survey will be anonymous and confidential to increase participation and honesty,^
41
^ consisting of a series of close-ended questions using a Likert scale, plus open-ended questions. The survey length, content, and mode of survey dissemination will be considered to maximise response.

##### Participants, sampling, and recruitment

The survey will target the same population as phase 1, front-line providers who work in health sites across country WA. This target population is made up of nursing services and medical officers/practitioners working directly with patients, often in acute or emergency situations, totalling approximately 6000 people. The survey will target this entire population via convenience and purposive non-probability sampling; a sample size of over 362 will ensure the results will be statistically significant, with a 95% confidence level and 5% margin for error.

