RE-AIM dimension	Expanded RE-AIM & IOF definition	Data measure	Data collection
Reach	Number of individuals exposed to the intervention	Number of CC patient contacts (by site, health facility type, region) for each command centre service	Service data
	Proportion of intended audience who participate in the intervention	Proportion of CC patient contacts compared to total health facility presentations	Service data
	Representativeness of individuals relative to the intended population	CC Patient contact characteristics (age group, sex, postcode, Aboriginal and/or Torres Strait Islander status, priority category, diagnosis)	Service data
Effectiveness	The degree to which the intervention is producing its intended effects while assessing potential unintended consequences and changes in quality of life	Degree to which staff agree that the intended objectives of the CC are being met	Survey Interviews
Adoption	Number of settings that participate in or are exposed to the intervention. (Organisational level)	Number of sites where CC services and infrastructure have been implemented (by health facility type and region) for each CC service	Service data
	Proportion of the intended settings who deliver or are exposed to the public health intervention. (Organisational level)	Number of sites actively using CC services compared to where services and infrastructure have been implemented by not being actively used. Determined by patient volume.	Service data
	Representativeness of settings relative to the intended population who participate in or are exposed to the public health intervention. (Provider level)	Number and characteristics of front-line providers using the CC (by site, health facility type, region) for each service	Survey
	Antecedent assessment of service recipient perception (Provider level)	Front-line provider attitudes and perceptions of CC services Normalisation MeAsure Development (NoMAD) questionnaire^ 39 ^	Interviews Survey
Implementation	Consistency of delivery as intended and in the time required across staff and organisations	Fidelity: Rollout of services according to implementation plan	Service data Interviews Project initiation documents Operational guidelines
	Adaptation Assessing indicators of adaptation prior to, during, and following implementation of the intervention	Local adaptations Cultural adaptations	Survey Interviews Project initiation documents Operational guidelines

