## Discussion

This paper describes the research protocol to evaluate the current implementation of the WACHS CC, a RPPT service, to explore factors for differential usage, and provide evidence-based recommendations for continual improvement. The CC's main aims are to increase access to acute, emergency, and specialist advice to those living in rural and remote areas, and to provide an additional layer of support for the place-based health workforce. As an emerging field of research, the results will contribute to a greater understanding of RPPT.

Innovative and sustained workforce models and solutions are needed globally, with virtual healthcare demonstrating potential especially in rural and remote areas to support and strengthen the local workforce,^60–63^ but are often not addressed in workforce retention strategies or reviews.^64–66^ The research outlined in this protocol will focus on the provider aspects that may influence the use of the suite of WACHS CC services. Specifically, the research will generate new knowledge to inform more strategic implementation via greater understanding of provider behaviours, attitudes, and perceptions, plus explore if the value and sustainment of these services can assist with workforce retention into the long term.

Sustainability and sustainment are often reported as the least researched implementation outcomes.^
67
^ This research will assist when selecting evidence-based strategies and adaptations for continual service improvement and optimisation of provider-to-provider virtual care models. The use of theories and frameworks in this research is intended to contribute to improving implementation at the local level, but to also be generalisable to the broader national and international context, to fill knowledge gaps and increase the evidence base of RPPT.

Strengths and limitations of this research are recognised. First, a non-randomised study design is chosen, which can produce risks of bias. This could include participant bias (social desirability of responses), sampling bias (volunteer bias and convenience sampling), and confounding bias. The ROBINS-I (Risk Of Bias In Non-randomised Studies – of Interventions) tool will be used throughout this research to identify and assess possible biases, plus as guidance to reduce bias in each domain included in the tool.^
68

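### The survey target of 362 is a simple-random-sampling precision figure, so it cannot guarantee statistical significance, and a non-probability sample does not carry the stated 5% margin

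*Protocol article*

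**What the plan says.** Under Phase 2, part 1 (survey), the subsection on participants, sampling and recruitment gives the target population as nursing and medical staff, "totalling approximately 6000 people". It then says: "The survey will target this entire population via convenience and purposive non-probability sampling". The second half of that sentence is the sample-size statement: "a sample size of over 362 will ensure the results will be statistically significant, with a 95% confidence level and 5% margin for error".

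Three other places bear on it:

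- **Data collection** (same part) describes an all-staff email with two reminders over 30 days, plus open channels such as posters with QR codes and social media. Respondents therefore select themselves.
- **Data analysis** (same part) plans descriptive summaries only. Inferential testing is mentioned for the Phase 1 service data, not for the survey.
- **Discussion** lists, among possible biases, "sampling bias (volunteer bias and convenience sampling), and confounding bias". It does not refer back to the survey margin.

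**The concern.** The sentence makes two promises, and neither follows from the number.

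The first is significance. Whether a result is significant depends on a hypothesis, the true size of the difference and the groups compared. A sample size chosen for interval width fixes none of these. If there is truly no difference, a 5% test is non-significant about 95% of the time at any sample size.

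The second is the margin. A sampling margin of error describes variation over repeated random draws from the population. Here no random draw is made, and who answers is decided by the staff themselves. Because the survey is about use of and attitudes to the service, willingness to answer may well be related to what is measured.

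What is at stake is how the survey is read. Its results feed the integration in Phase 3 and the recommendations, and the authors intend them to inform wider settings. Stated this way, reaching the target could be taken as evidence of accuracy that the design cannot supply.

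**Working it through.** **Inputs from the article:** N about 6000; target 362; 95% confidence (z = 1.96); margin e = 0.05. **Assumed:** p = 0.5, the usual worst case.

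**1. Reproduce the figure.**

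- Without correction: n0 = z² p(1−p)/e² = 1.96² × 0.25/0.05² = 384.16.
- With finite-population correction: n = n0/[1 + (n0 − 1)/N] = 384.16/(1 + 383.16/6000) = 361.1, rounded up to 362.
- Check: half-width at 362 = 1.96 × √[(0.25/362) × (6000 − 362)/5999] = 0.0499, or 4.99 points.

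The arithmetic is right. The inputs are a confidence level, a margin, a proportion and a population size; none is an effect size or a power. The result is valid for one whole-sample proportion under simple random sampling.

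**2. Does 362 guarantee significance?** No survey test is planned, so this is only an illustration. Assume two equal groups of 181, 50% in one group, two-sided 5%. Power = Φ[(d − 1.96 × SE0)/SE1], with SE0 pooled and SE1 unpooled.

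| True difference d | Power |
|---|---|
| 5 points | 16% |
| 10 points | 48% |
| 15 points | 83% |

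The chance of a significant result depends on the unknown difference; the sample size does not settle it.

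**3. Does the 5-point margin hold?** With response fraction r, the bias of the respondents' proportion is (1 − r) × gap, where the gap is responders minus non-responders. At the minimum target r = 362/6000 = 0.0603, so 1 − r = 0.9397. The gap that alone uses up the whole 5 points is 5/(1 − r). Response levels above the target are assumed, to show the range.

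| Responses | r | Gap giving a 5-point bias |
|---|---|---|
| 362 | 6.0% | 5/0.9397 = 5.3 points |
| 1500 | 25% | 5/0.75 = 6.7 points |
| 3000 | 50% | 5/0.50 = 10.0 points |

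The same thing seen through response propensity: assume a true proportion of 50%, and let staff with a favourable view be R times as likely to answer. The expected estimate is R/(R + 1).

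| R | Expected estimate | Bias |
|---|---|---|
| 1.25 | 55.6% | 5.6 points |
| 1.5 | 60.0% | 10.0 points |
| 2 | 66.7% | 16.7 points |

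For a given R this bias does not depend on n, so reaching the target does nothing to reduce it.

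**4. Reach of the nominal margin.** Even under simple random sampling it covers the whole sample only. With an assumed even split over seven regions, 362/7 = 51.7 and 1.96 × √(0.25/51.7) = 0.136, or 13.6 points.

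**The case against.** The strongest reply is that this is a wording fault in a descriptive staff survey. The number reproduces, no test or decision rule depends on the sentence, interviews and triangulation follow, and the Discussion openly names volunteer and convenience sampling. Also, 362 is a floor: everyone is invited, with reminders and several channels, so 94% non-response is the worst case that still meets the target. Much of this stands. It limits the remedy to the sentence itself and means the bias figures are illustrations, not forecasts. But a general limitation elsewhere does not correct a specific guarantee, and a descriptive plan leaves the significance claim with nothing to attach to.

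A reader might infer more than the article supports:

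- *That clustering of staff in facilities widens the margin by a known factor.* The whole population is invited and there is no cluster-sampling stage. Under the simple random sampling that the formula assumes, similarity within facilities does not inflate the variance of an overall proportion. Clustered response could matter, but the article gives no figures from which to derive a design effect.
- *That the article promises 5 points within subgroups.* Table 2 asks for "Number and characteristics of front-line providers using the CC (by site, health facility type, region) for each service", but as a descriptive breakdown with no stated precision. The 13.6 points contradicts nothing in the text; it only shows why the restated sentence should confine the margin to the whole sample.
- *That low power damages a planned analysis.* No survey test is planned.
- *That missing weighting or clustered standard errors is a fault.* A full protocol or analysis plan commonly holds such detail. Weighting by profession, region and facility type would not remove self-selection on attitude within those groups in any case.

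**Conclusion.** The sentence is wrong as written in both halves. The target was derived for interval width and cannot guarantee significance. The margin presumes random sampling, which the sentence itself rules out.

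The reproduction of 362 is firm, given p = 0.5. How far the true error exceeds 5 points cannot be known from the article: it depends on how responders and non-responders differ, for which the article gives no figure. What can be said is that, at the minimum target, a modest gap would be enough to match the whole claimed margin. The fault lies in the inference drawn from the number. It is no reason to call the sample too small or the recruitment plan unsound.

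**What to change.** Delete the significance claim and restate the sentence along these lines:

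> 362 responses would give about ±5 percentage points, at 95% confidence, for one overall proportion under simple random sampling from 6000. Because sampling is non-probability, 362 is a recruitment target only; the nominal margin does not cover non-response or self-selection, and does not apply to breakdowns by region, facility type or site.

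Neither the target, the recruitment routes nor the planned descriptive analysis has to change. The work is one sentence, and the price is that the stated precision looks less favourable.

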##### Data collection

The survey will be conducted online using Qualtrics (Qualtrics XM, Provo, UT) and distributed via the internal WACHS Global email. The survey will be open for a 30-day period, with a follow-up email reminder sent out on days 7 and 14. Additional modes of recruitment will be guided by the advisory research group, including dissemination and promotion by regional stakeholders, posters with QR codes, social media posts, and targeted email lists. Participants will be provided with a participant information sheet and consent prior to completing the survey, with the option to withdraw at any stage.

On completion of the survey, participants can indicate if they would like to be involved in the continuing research (interviews). These details will be collected in a separate database, keeping survey responses non-identifiable, accessed by the researcher only for follow-up interviews.

##### Data analysis

Survey data will be analysed using descriptive statistics, including measures of frequency, central tendency, and range of variation.^
41
^

#### Phase 2, part 2: semi-structured interviews

Individual interviews will be used to provide a deeper understanding of behaviours, attitudes, perceptions, and value. The interviews will be semi-structured with an interview guide developed using the expanded RE-AIM framework and NPT as theoretical basis. This interview guide will be piloted with the research advisory team and a small number of CC staff to ensure comprehension, ease of response, and flow.

##### Participants, sampling, and recruitment

Survey respondents who indicate they would like to participate in follow-up individual interviews will be contacted by the researcher via email. Sample size will be dependent on a judgement of data adequacy and representativeness across clinician groups and location by the researcher.^50–52^ In the case of a large number of respondents, the researcher will seek advice from the supervisory and advisory teams and consider alternative options, such as focus groups. Regardless, all participants will be contacted if they have expressed interest. In the case of a low number of respondents, the advisory research group will guide additional modes of recruitment via purposive, convenience, and snowball sampling methods.

##### Data collection

Interviews will be conducted via Microsoft Teams by the researcher, scheduled for 30 min, recorded, and transcribed via Teams. Participants will be provided with a participant information sheet and consent prior to commencing the interviews, with the option to withdraw at any stage. Interview transcripts will be checked by the researcher for accuracy immediately after each interview. Transcripts may contain references to names, roles or contexts that could potentially identify participants or others in the organisation. Transcripts will be carefully reviewed to remove or generalise any potentially identifying information. All reporting will be done in an aggregate or non-identifiable manner. All data and analysis will be conducted in a secure and controlled environment.

##### Data analysis

Analysis of data collected from interviews will be analysed using the NVIVO software, guided by the Braun and Clarke^
51
^ reflexive thematic analysis. This type of analysis is an organic, fluid, and flexible approach, including both inductive and deductive analysis. This allows a deeper engagement and understanding with the data and any contextual information to be interpreted.^
53
^ Data will first be analysed inductively, with coding and theme development directed by the content of the data. This research is looking to test and validate findings from phase 1 and phase 2, part 1, so refining themes will also take a deductive approach in phase 3, where analysis is then directed by existing concepts and ideas, along with the expanded RE-AIM framework and NPT. A six-phase process will guide the reflexive thematic analysis: (a) Familiarisation with the dataset; (b) Coding; (c) Generating initial themes; (d) Developing and reviewing themes; (e) Refining, defining and naming themes; and (f) Writing up.^
54
^ The lead researcher will undertake the open and organic coding and theming through reflexive thematic analysis, as recommended by Braun and Clarke, which differs from codebook and coding reliability thematic analysis.^
51
^ Inductive reflective thematic analysis removes pre-conceived ideas and themes from the data, as much as possible. The tool developed by Braun and Clarke^
53
^ for evaluating thematic analysis will be used as a reflective guide throughout phase 2, part 2.

#### Phase 3: interpretation and testing of results

The purpose of phase 3 is to integrate results from phases 1 and 2 to develop evidence-based strategies and recommendations for the value and sustainment of RPPT. The RE-AIM framework^
34
^ will be used to frame the integration of data, with two points of data integration.^
55
^ The first point will be post-survey where quantitative and qualitative survey data will be integrated with service data to illustrate and explain service data. The second point of integration will be post-interviews, where the qualitative interview data are integrated to determine if there is a convergence of data, plus to illustrate and explain differential use of CC services.

Results of this interpretation will be used to identify barriers and enablers, including context-specific factors to improve the implementation and sustainment of the CC services.^
56
^ Stakeholder feedback and participation is essential to prioritise and make implementation and optimisation systematic.^
56
^ Stakeholder participation will occur via a deliberative dialogue forum with WACHS CC stakeholders to deliver results of the research, plus validate any interpretations or conclusions drawn from the research. Deliberative dialogue forums have been used widely in public health and health policy research as a formal process of interactive knowledge translation and exchange, also increasing the prospect of research translation and implementation.^
57
^

Participants will be invited via email through purposive and convenience sampling, and advice from the research advisory group. Participants will include front-line clinicians, CC staff, WACHS executive and managerial representatives, and WACHS staff involved in virtual health policy. The forum, informed by Boyka et al.^
58
^ recommendations, will be delivered face-to-face by the researcher and advisory team, with optional online attendance for rural and remote participants, for a maximum of 3 hours.

The deliberative forum will follow an implementation mapping style approach as defined by Fernandez et al.^
59
^ Implementation mapping is a systematic process, adapted from intervention mapping, which will be used to guide the development, selection, and tailoring of strategies to improve the adoption, implementation, and maintenance of CC services.^
59
^ Implementation mapping will follow a five-step process, mapped to the phases of this research:
Conduct an implementation needs assessment and identify program adopters and implementers.
Phase 1 and 2State adoption and implementation outcomes and performance objectives, identify determinants, and create matrices of change objectives.
Phase 2 and 3Choose theoretical methods (mechanisms of change) and select or design implementation strategies.
Phase 3Produce implementation protocols and materials.
Phase 3Evaluate implementation outcomes.
Phase 3.A final technical document will be produced for internal use with a summary of research findings, insights, tailored strategies, recommendations, and setting up of a long-term monitoring framework. The report will be easily comprehensible and provided to all interested WACHS staff.

## Discussion

This paper describes the research protocol to evaluate the current implementation of the WACHS CC, a RPPT service, to explore factors for differential usage, and provide evidence-based recommendations for continual improvement. The CC's main aims are to increase access to acute, emergency, and specialist advice to those living in rural and remote areas, and to provide an additional layer of support for the place-based health workforce. As an emerging field of research, the results will contribute to a greater understanding of RPPT.

Innovative and sustained workforce models and solutions are needed globally, with virtual healthcare demonstrating potential especially in rural and remote areas to support and strengthen the local workforce,^60–63^ but are often not addressed in workforce retention strategies or reviews.^64–66^ The research outlined in this protocol will focus on the provider aspects that may influence the use of the suite of WACHS CC services. Specifically, the research will generate new knowledge to inform more strategic implementation via greater understanding of provider behaviours, attitudes, and perceptions, plus explore if the value and sustainment of these services can assist with workforce retention into the long term.

Sustainability and sustainment are often reported as the least researched implementation outcomes.^
67
^ This research will assist when selecting evidence-based strategies and adaptations for continual service improvement and optimisation of provider-to-provider virtual care models. The use of theories and frameworks in this research is intended to contribute to improving implementation at the local level, but to also be generalisable to the broader national and international context, to fill knowledge gaps and increase the evidence base of RPPT.

Strengths and limitations of this research are recognised. First, a non-randomised study design is chosen, which can produce risks of bias. This could include participant bias (social desirability of responses), sampling bias (volunteer bias and convenience sampling), and confounding bias. The ROBINS-I (Risk Of Bias In Non-randomised Studies – of Interventions) tool will be used throughout this research to identify and assess possible biases, plus as guidance to reduce bias in each domain included in the tool.^
68
^ The mixed methods design, theoretical frameworks, and a reflexive thematic analysis technique are employed throughout research design, data collection, and data analysis. These have been shown to be useful in complex healthcare settings and long-term sustainment approaches, assisting with data interpretation and reducing bias.^69,70^ Additionally, the researcher is independent of WACHS and will make this clear in the survey and interviews, while ensuring participant confidentiality.

Second, this research is focused on the perspective of the front-line providers who work with patients in rural and remote areas, and how the services can be of benefit. Although patient episode data will be captured, which outlines the extent of implementation and access status, the consumer perspective is therefore out of scope, but recommended for future research to capture a more holistic view.

Third, the suite of clinical CC services was implemented at various times and locations, with varying data collection platforms and data fields. To combat this, data will be analysed using the same data variables, allowing for comparison across services.

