^ identified key knowledge gaps and specific recommendations to build evidence on the emerging use and effects of RPPT. Highlighted was the inconsistent evaluation, implementation, and sustainment of these services, recommending that conceptual frameworks be used, and contextual factors be considered. Additionally, Wakefield et al.^
20
^ calls for new research efforts to understand the value and effects these services deliver, with an aim to improve health outcomes for rural and remote patients, by supporting the local workforce and improving access to healthcare.

This research intends to strengthen the evidence base of RPPT by providing methodologically sound research to fill knowledge gaps and recommendations identified by Totten et al.^
19
^ and Wakefield et al.^
20
^ Recommendations identified by these authors^
20
^ that this research intends to cover include:
The variation of uptake across diverse settings, organisational structures, and provider types.The standardisation of measures across multiple sites to assess outcomes and impact.Evaluate whether RPPT impacts rural provider recruitment and retention.Engage providers to shape and evaluate RPPT to better meet community and population needs.Examine sociocultural factors that may influence uptake, outcomes, and sustainability.Use statistical approaches to minimise selection bias and address confounding effects.Employ mixed methodologies to triangulate qualitative and quantitative results.Specifically, this research will utilise the Western Australia Country Health Service (WACHS) Command Centre (CC) as an example of RPPT , to assess the differential implementation of RPPT across over 100 sites in country Western Australia (WA). The CC operates 24 h a day, 7 days a week, specialising in emergency, acute, and specialty clinical services, and staffed by clinical and non-clinical staff who support over 6000 front-line providers in country WA.^
23
^ The purpose of the CC is to virtually support the delivery of, and equitable access to, high-quality healthcare for people in country WA, and to complement place-based service provision.

Therefore, the overall aim of this research is to increase the understanding of provider-to-provider telehealth in rural and remote settings, including its value, benefit, and sustainment, in the WACHS.

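### The survey's acknowledged volunteer bias is met with ROBINS-I and descriptive statistics, neither of which adjusts pooled workforce results for who responds

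*Protocol article*

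**What the plan says.** In the protocol article, the section on rural provider-to-provider telehealth lists recommendations from earlier work that the research intends to cover. One is: "Use statistical approaches to minimise selection bias and address confounding effects".

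Under the survey's participants and sampling: "The survey will target this entire population via convenience and purposive non-probability sampling", a group "totalling approximately 6000 people". The same sentence continues that "a sample size of over 362 will ensure the results will be statistically significant, with a 95% confidence level and 5% margin for error".

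Phase 2 is described as "employing a cross-sectional survey and follow-up individual interviews". The whole of the stated survey analysis is: "Survey data will be analysed using descriptive statistics, including measures of frequency, central tendency, and range of variation".

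The first limitation in the Discussion lists social desirability, then "sampling bias (volunteer bias and convenience sampling), and confounding bias". It names ROBINS-I, spelled out there as a risk-of-bias tool for non-randomised studies of interventions, and says that this "tool will be used throughout this research to identify and assess possible biases, plus as guidance to reduce bias in each domain" that it includes. The same limitation goes on to credit the mixed methods design, the theoretical frameworks and reflexive thematic analysis with reducing bias, and cites the researcher's independence and participant confidentiality. The survey sections add anonymity, attention to length and mode of dissemination, and email reminders on days 7 and 14.

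**The concern.** The plan names a specific bias, signals a statistical response to it, and then states a tool and an analysis that do not supply one. ROBINS-I, on the title the article gives it, appraises studies of interventions. The survey has one group and no comparator, so there is no intervention-effect estimate to appraise. A rating of bias also leaves a percentage as it was.

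This matters because the Phase 1 service data hold no individual staff data, so the survey is the quantitative source on provider-level use. Table 2 takes the number and characteristics of providers using the Command Centre from it, under a definition of representativeness. The 5% margin shows that inference to about 6000 staff is intended. Recruitment through regional stakeholders, posters and targeted email lists can make response uneven by profession, facility type and region. Use may well differ along the same lines: services are enabled in 87 of 103 facilities, and most smaller sites are run by generalist nurses. If so, a pooled percentage describes the respondents rather than the workforce.

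**Working it through.** **The plan's own figure.** Inputs from the survey sampling section: N = 6000, 95% confidence, margin 0.05. The proportion is not stated, so p = 0.5 is assumed.

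- n0 = 1.96² × 0.25 / 0.05² = 384.15 (unrounded z)
- n = 384.15 / (1 + 383.15/6000) = 361.09, rounded up to 362

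The figure is reproduced. The margin at n = 362 with finite population correction is 4.99 points. It measures random sampling error only and contains nothing for unequal response. 362/6000 = 6.0%, which is the minimum response sought, not a forecast.

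**Bias of a pooled percentage under unequal response.** The documents give no use or response rates by stratum, so these are assumptions: two equal halves of the workforce, with use of 20% (larger hospitals) and 70% (smaller sites), and an overall response of 6%.

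- True pooled use = 0.5 × 0.20 + 0.5 × 0.70 = 45.0%
- Observed pooled use = (0.5·r1·0.20 + 0.5·r2·0.70) / (0.5·r1 + 0.5·r2)

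| Response r1 v r2 | Calculation | Observed | Bias |
|---|---|---|---|
| 5% v 7% | (0.005 + 0.0245)/0.06 | 49.2% | +4.2 points |
| 4% v 8% | (0.004 + 0.028)/0.06 | 53.3% | +8.3 points |

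The result depends on the ratio r2/r1 (1.4 and 2.0), not on the level. A higher response at the same ratio gives the same bias, so reminders alone need not help. Within each half the observed use stays at 20% and 70%.

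**What weighting does here.** Weighting each half back to its 50% share returns 0.5 × 0.20 + 0.5 × 0.70 = 45.0%. The price is the design effect, Σ(sample share × w²), with w = population share / sample share:

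- 5% v 7%: shares 0.417 and 0.583, weights 1.20 and 0.857, design effect 0.600 + 0.429 = 1.029; margin at n = 362 is 4.99 × √1.029 = 5.1 points
- 4% v 8%: shares 0.333 and 0.667, weights 1.50 and 0.75, design effect 0.750 + 0.375 = 1.125; margin 4.99 × √1.125 = 5.3 points

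Weighting on three factors would cost more. Assumed design effects of 1.2, 1.5 and 2.0 give margins of 5.5, 6.1 and 7.1 points.

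**What weighting does not do.** If users volunteer more readily than non-users within a stratum, with response ratio R, the observed proportion is pR/(pR + 1 − p). At true use of 50%, R = 1.25 gives 0.625/1.125 = 55.6%, and R = 2 gives 1/1.5 = 66.7%. Headcount weights leave this part in place.

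**The case against.** A reader might infer that ROBINS-I is the only safeguard named. It is not. The same limitation and the survey sections name anonymity, reminders, survey design, mixed methods, theoretical frameworks and researcher independence. What remains is narrower: these act on honesty, interpretation or the volume of response, and none adjusts for its composition.

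A reader might also infer that survey percentages will certainly be reported uncorrected. The article does not say so. It is condensed, and a weighting plan may sit in a fuller document. The point therefore rests on what is stated, a descriptive analysis and an ill-fitting tool set against an expressed intention, and not on missing detail.

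Three further objections have weight. The intention to use statistical approaches appears in a list of others' recommendations and is not tied to the survey. ROBINS-I is offered for assessment and guidance across the whole project, and the article never claims that it corrects percentages; that it does not fit a one-group survey is inferred from its title. And Table 2 reports provider use by site, facility type and region, so the illustrated bias does not touch those stratified results. These points limit the finding to pooled figures but do not remove it: the article gives no other method for the selection bias it acknowledges. Phase 1 does compare contact counts by region, facility type and site, but those comparisons are not intervention effects either.

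**Conclusion.** The point holds in limited form and should be acted on. The protocol expresses an intention to minimise selection bias statistically and acknowledges volunteer bias, but the survey analysis it states is descriptive only and the bias tool it names does not suit a one-group cross-sectional survey. Pooled workforce percentages and scale scores are exposed if response differs by profession, facility type or region. In the illustration the error is 4 to 8 points, comparable with or larger than the 5-point margin claimed. That size rests wholly on assumed shares, use and response rates. It shows that the mechanism can matter, and it does not forecast this survey's bias.

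**What to change.** In the Discussion, do not rely on ROBINS-I to control selection bias in the survey. In the survey's data analysis section, state that:

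1. respondents will be compared with WACHS headcounts by profession, facility type and region;
2. pooled percentages and scale scores will be shown weighted to those headcounts, beside the unweighted results;
3. early and late responders will be compared, for which the day-7 reminder gives a natural cut;
4. self-selection within strata remains and cannot be removed by weighting.

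A comparison with Phase 1 contacts by facility type and region is optional. It is ecological only, because contacts count patients and not staff, and it partly overlaps with the survey and service data integration already planned for Phase 3.

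The cost is one headcount table (assumed obtainable from the employer), a short added analysis, somewhat wider intervals, and the need to collapse very small strata.
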